## Abstract

**Background:**

Although pulmonary rehabilitation is helpful for patients following lung cancer surgery, rehabilitation is not widely available, due in part to a lack of medical resources. Recent developments in digital health care have overcome the space limitations associated with in-person health care. This study will evaluate and compare the efficacy of three different smartphone healthcare systems in patients with lung cancer.

**Methods:**

This single center randomized controlled study is designed to evaluate the efficacy of digital healthcare applications for lung cancer patients after thoracoscopic lung resection. A total of 320 patients will be enrolled and randomized 1:1:1:1 into four different groups, with one group each using the smartphone applications NOOM, Walkon, and Efilcare and the fourth being the control group without intervention. Questionnaires will be administered to patients at baseline and after 3, 6, and 12 months. The primary endpoint will be the score on the EuroQol five-dimension index. Secondary endpoints will include other questionnaires about quality of life and dyspnea.

**Discussion:**

This prospective randomized controlled study may allow assessments and comparisons of the efficacy of various smartphone applications in patients who undergo lung cancer surgery. This process may enable the introduction of healthcare interventions that maintain quality of life in patients with lung cancer.

*Trial registration* CRIS, KCT0005447. Registered 06 October 2020, https://cris.nih.go.kr/cris/search/detailSearch.do/19346

## Background

Lung cancer is one of the most commonly diagnosed malignancies and the leading cause of cancer-associated deaths worldwide [1]. The overall survival of patients with lung cancer has been significantly improved by the use of surgery, neoadjuvant and/or adjuvant chemotherapy, and radiotherapy, with survival being especially improved in patients with early stage non-small cell lung cancer [1]. Although survival is the most important goal, maintaining of quality of life and exercise capacity are also important. Increased exercise capacity and better quality of life have been associated with favorable long-term outcomes in various diseases [2–4]. Surgical resection of lung tumors reduces lung volume, resulting in reduced exercise capacity and poorer quality of life. Perioperative management of lung cancer patients should therefore focus on quality of life [5–7]. Pulmonary rehabilitation of patients who have undergone lung resection was found to improve their exercise capacity, pulmonary function, and quality of life [8, 9]. Pulmonary rehabilitation, however, is limited by a scarcity of medical resources and difficulties supervising adequate pulmonary rehabilitation [10].

Proper diet and exercise after anti-cancer treatment are important for lung cancer patients [11–13]. Although the ability of clinicians to supervise pulmonary rehabilitation and provide education about diet is limited by lack of time and interest, digital interventions are regarded as effective alternatives to in-person management [14–17]. Digital interventions through smartphone applications are preferred owing to easy accessibility and expandability, including the ability of these applications to provide a direct coaching system and important information [18]. Although most studies assessing the efficacy of smartphone applications have been performed in patients with chronic diseases, these applications may also help patients with lung cancer who plan to undergo surgery and require postoperative lifestyle management.

The present study is designed to evaluate the efficacy of smartphone healthcare applications for lung cancer patients following thoracoscopic lung resection. Three smartphone applications and a control group will be compared using the results of pulmonary function tests and exercise capacity, as well as questionnaires related to patient quality of life and psychological distress.

## Methods/design

### Study design

This study is designed as a single center randomized controlled study evaluating the efficacy of digital healthcare applications for lung cancer patients who undergo thoracoscopic lobectomy. Patients will be recruited at Asan Medical Center, a university affiliated 2700-bed tertiary medical center. A total of 320 patients will be enrolled. The study duration is 1 year, and all enrolled patients will be evaluated at outpatient clinics by attending clinicians at baseline and at 3, 6, and 12 months after surgery. The study protocol has been approved by the Institutional Review Board of Asan Medical Center (IRB no. 2020-1015), and written informed consent will be obtained from all participants by attending investigators and research assistants.

### Study participants

Patients scheduled to undergo a planned thoracoscopic lobectomy for lung cancer will be screened by attending clinicians. Patients will be included if they (1) are aged 20–70 years; (2) have been pathologically diagnosed with primary lung cancer; (3) are scheduled for lobectomy with a thoracoscope; (4) have no evidence of lymphatic or distant metastasis; and (5) provide written informed consent. Patients will be excluded if they (1) have any evidence of metastasis; (2) have a history of segmentectomy or wedge resection for lung cancer; (3) are changed to open thoracotomy during surgery; (4) are scheduled for neoadjuvant or adjuvant chemotherapy or radiotherapy around the time of surgery; (5) are pregnant or breast-feeding; (6) have a chronic respiratory disease, including asthma, pulmonary tuberculosis or chronic obstructive pulmonary disease; (7) have a history of diagnosis of other malignancies within 5 years; and (8) have a disability that would make exercise difficult. Adequate patients will be enrolled in this study based on the attending physicians’ and corresponding author’s judgements.

### Randomization and intervention

The study flow is presented in Fig. 1. The enrolled patients will be stratified according to gender and forced expiratory volume in 1 s (≥ 60% or < 60% of the predicted normal value). The patients will be subsequently randomized 1:1:1:1 to four groups. Allocation to the control or intervention group will be based on the pre computer-generated random number list by a statistician. Following thoracoscopic lobectomy for lung cancer and stabilization, all enrolled patients will participate in education sessions for pulmonary rehabilitation. During these sessions, specialists will teach methods of stretching, aerobic exercise, and muscle training, and recommend an adequate diet [10]. In group A, patients will use the smartphone application NOOM, for 12 weeks. After that, the patients will try to maintain the modified lifestyle. Patients will use Walkon in group B and Efilcare in group C during study periods. Patients in group D will be the control group without any intervention. Enrolled patients will undergo the measurement and questionnaires at index date and after 3, 6, and 12 months. During each visit, attending clinicians will motivate and educate the patients. Allocation concealment will be guaranteed by opaque, sealed envelopes.

**Fig. 1 Fig1:**
[figure not shown]
Study flow

### Digital intervention with smartphone applications

The NOOM, Walkon, and Efilcare smartphone applications are illustrated in Fig. 2. NOOM is a worldwide application in which users initially record their gender, height, weight, and age and set a target body weight. The application introduces adequate methods of diet and exercise. Users continuously record their body weight and patterns of diet and exercise. Based on these records, human coaches regularly contact the users for supervision and advice via messages.

**Fig. 2 Fig2:**
[figure not shown]
Description of the three smartphone applications tested in this study. (left) NOOM, (center) Walkon, (right) Efilcare

The Walkon application measures step counts, and the intensity of walking exercise based on time and velocity. It also encourages users by displaying ranking based on walking record, recommending suitable routes for walking, and providing various benefits as compensation.

Users of the Efilcare application record their underlying disease, degree of stress, diet and exercise patterns, body weight, body temperature, blood glucose, and blood pressure. Based on these parameters, the application recommends proper methods of exercise and provides pre-written information, including about lung cancer.

### Data collection and study outcome

At screening, researchers will record patients’ baseline characteristics, including age, sex, smoking history, European Cooperative Oncology Group Performance Status, underlying disease, and previous cancer history. In addition, lung cancer-related information, including pathologic diagnosis, clinical and pathologic stage, and surgery record, will be recorded.

The primary study endpoint will be score on the EuroQol five-dimension (EQ-5D) index, which measures patient quality of life [19]. Secondary endpoints will include body weight and body mass index, as well as measures of pulmonary function and exercise capacity, such as pre- and post-bronchodilator pulmonary function tests, diffusion capacity and 6-min walk tests. Other secondary endpoints will include quality of life questionnaires to evaluate quality of life (Distress Thermometer, Health-Related Quality of Life Instrument with 8 Items, Patient Health Questionnaire-9, Fear of Progression Questionnaire-Short Form, Cancer-related Dysfunctional Beliefs about Sleep, Insomnia Severity Index) and dyspnea degree (modified Medical Research Council dyspnea scale). The timeline of data collection is presented in Table 1.

**Table 1 Tab1:** Timeline of data collection

	Screening and enrollment Index date	Visit 1 3 months	Visit 2 6 months	Visit 3 12 months
Medical history	●			
Chest CT and laboratory tests	●	●	●	●
Informed consent	●			
Body measurements	●	●	●	●
PFT and 6MWT	●	●	●	●
Questionnaires	●	●	●	●

*6MWT* 6-min walk test, *CT* computed tomography, *PFT* pulmonary function test

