### Sample size calculation

We assumed for sample size calculation that effective postoperative rehabilitation could restore the quality of life to a similar level before surgery. A previous lung cancer study showed that the preoperative and postoperative EQ-5D indices were 0.81 ± 0.19 and 0.74 ± 0.11, respectively [20]. Additionally, a minimal clinically important difference in EQ-5D has been observed between 0.03 and 0.05 [21]. Because patients were classified into four groups, the margin of type 1 error was set at 0.008. Calculations showed that a minimum of 76 patients in each group was required to detect a significant difference at the 0.008 level with a power of 0.9 and a dropout rate of 25%.

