### Statistical analysis

SAS (SAS Institute Inc., Cary, NC) and R (version 4.1.2; R Development Core Team, Vienna, Austria) software will be used for all statistical analyses. Continuous variables will be presented as means ± standard deviations or median [interquartile range] and compared by Student’s *t*-test or the Mann–Whitney U-test. Categorical variables will be presented as numbers and percentages and compared by the χ^2^ test or Fisher’s exact test. All tests of significance will be two-sided, with *P* < 0.05 defined as statistically significant.

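### The primary EQ-5D endpoint names no deciding visit, and the 0.008 level allows for four groups but not for three follow-up visits

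*Protocol article*

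**What the plan says.** The endpoint is stated twice in the protocol article. Data collection and study outcome says: "The primary study endpoint will be score on the EuroQol five-dimension (EQ-5D) index, which measures patient quality of life". The abstract says: "The primary endpoint will be the score on the EuroQol five-dimension index". Neither place gives a visit, a change from baseline or a summary over visits.

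The measurement schedule is clear: "Questionnaires will be administered to patients at baseline and after 3, 6, and 12 months". Table 1 and the randomization section agree with it.

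On the error rate, Sample size calculation says: "Because patients were classified into four groups, the margin of type 1 error was set at 0.008". It states no divisor and lists no comparisons. The planning difference there contrasts a preoperative with a postoperative mean and gives no postoperative time point.

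Statistical analysis names two-group tests (Student's t or Mann–Whitney for continuous data), with no visit and no model over visits. It adds "All tests of significance will be two-sided", with P below "0.05 defined as statistically significant".

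**The concern.** A primary endpoint measured at three follow-up visits needs either a deciding visit or a rule for combining the visits. Without one, the planned significance level has no defined set of tests to protect. Here the level was lowered to allow for four groups, and nothing in it allows for three visits. If each visit is tested, or the most favourable one is reported as primary, the chance of a false claim for at least one comparison can exceed 5% even when 0.008 is applied.

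Two features of the trial make this matter. The outcome is patient-reported and the control group has no app, so patients will know whether they have one. The visit also changes the question: under Randomization and intervention, NOOM is used for 12 weeks, whereas Walkon and Efilcare are used throughout the study. A comparison among the apps at 12 months is therefore not the same comparison as at 3 months.

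**Working it through.** **Inputs from the protocol article**

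- Four groups, allocated equally (abstract): 4 × 3 / 2 = 6 pairs.
- Follow-up visits with EQ-5D: 3 (abstract and Table 1).
- Planning level: 0.008 (Sample size calculation), two-sided (Statistical analysis).
- The Discussion says that the apps are to be compared with one another as well as assessed for efficacy. This supports counting six pairs, but no section says that all six are confirmatory.

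**Assumption not in the article:** the correlation of EQ-5D between visits. It is varied from 0 to 0.95 and taken as equal for every pair of visits.

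**Step 1. The plan's own level.** 0.05 / 6 = 0.00833, which agrees with the stated 0.008. The divisor of six is an inference.

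**Step 2. One visit, six pairs.** Bonferroni bound: 6 × 0.008 = 0.048. Simulated under no difference between groups, allowing for the groups that the pairs share: about 0.040. So 0.008 does its job if one visit is fixed in advance.

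**Step 3. Three visits, six pairs.** 6 × 3 = 18 tests. Bonferroni bound: 18 × 0.008 = 0.144. If all 18 tests were independent: 1 − (1 − 0.008)^18 = 0.135. The tests are not independent, so the relevant figures are the simulated ones (400,000 runs for each correlation, no true difference, z-tests, equal groups):

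| Between-visit correlation | Six pairs, three visits, 0.008 | Three app-versus-control pairs, three visits, 0.008 | One pair, three visits, 0.008 |
|---|---|---|---|
| 0 | 11.5% | 6.4% | 2.4% |
| 0.5 | 10.4% | 5.9% | 2.2% |
| 0.7 | 9.3% | 5.3% | 2.0% |
| 0.8 | 8.5% | 4.8% | 1.8% |
| 0.9 | 7.1% | 4.1% | 1.5% |
| 0.95 | 6.2% | 3.5% | 1.3% |

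With six pairs, the error is above 5% at every correlation tried. With only the three app-versus-control pairs, it falls below 5% from a correlation of about 0.8.

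**Step 4. Separating out the general 0.05 level.** At P < 0.05, six pairs at a single visit already give about 20%. Over three visits the figure is about 28% (correlation 0.95) to 49% (correlation 0). Much of that excess comes from using 0.05 in place of 0.008, not from the missing visit, so these figures do not measure the present point.

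**Step 5. The price of keeping all 18 tests.** Bonferroni would need 0.05 / 18 = 0.0028 per test. Use n = 2 × SD² × (z for the two-sided level + z for power)² / difference², with difference 0.81 − 0.74 = 0.07, power 0.9 and the smaller of the two stated SDs, 0.11:

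- At 0.008: 2 × 0.0121 × (2.652 + 1.282)² / 0.0049 gives 77 evaluable patients per group.
- At 0.0028: 2 × 0.0121 × (2.991 + 1.282)² / 0.0049 gives 91.

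The trial enrols 320 / 4 = 80 per group before any dropout, so testing everything does not fit the planned size.

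**The case against.** The strongest reply is that the harm is conditional. A reader might infer that the article sets up 18 equally primary tests and that the 5% error is therefore already lost. The text does not support that. Statistical analysis is a general list of tests and does not say that every visit will be tested. A single visit named in advance, or a single test over all visits, would cause no inflation. The article is also a condensed account; a full protocol, analysis plan or registry entry may name the visit, and that cannot be checked here. This objection stands, and it limits the point to what the article leaves open.

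Second, six pairs is a reading of 0.008, not a statement in the plan. This also stands. With three app-versus-control pairs the excess is small, and at high correlation it disappears. Against that, 0.008 fits six pairs far better than three, and the Discussion intends comparisons among the apps.

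Third, a reader might conclude that month 3 must be the deciding visit because all three apps are in use then. The article does not establish this. NOOM runs for 12 weeks (84 days), three months is about 91 days, and the start of app use is not given. Visits are counted from surgery in Study design but from the index date in the randomization section and Table 1. The abstract's aim of maintaining quality of life, the maintenance period after NOOM and the Discussion's emphasis on sustained management all point towards a later visit.

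What the objections do not remove is that the article states the primary endpoint twice, and sets a sample size and a significance level for it, without fixing which measurement decides the trial.

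**Conclusion.** The concern holds in conditional form. The primary endpoint has no deciding visit, change or summary over time, and the 0.008 level allows for groups only. If all three visits are tested at 0.008, or the visit is chosen after seeing data, the family-wise error over six pairs rises from about 4% to about 6% to 12%. This rests on two assumptions: that 0.008 stands for 0.05/6, and that the between-visit correlation lies between 0 and 0.95. For the three app-versus-control pairs alone the range is about 3.5% to 6.4%.

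A reader might quote the much larger error at P < 0.05 as the size of this problem. That would be wrong, because about 20% is already present at one visit and comes from the separate conflict between 0.008 and 0.05. The matter should be settled before the data are looked at; recruitment has been under way since November 2020.

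**What to change.** Before data are looked at, state the following:

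1. One confirmatory EQ-5D variable: the index at one named visit, or one summary over the visits. Month 3 is one option, as it falls at or near the end of the 12-week NOOM period. The sponsor should choose to match its aim, since the article also points to maintenance over the year.
2. The comparison of groups on that variable, adjusted for the index-date EQ-5D in place of an unadjusted two-group test.
3. That EQ-5D at the remaining visits is secondary.
4. Which pairwise comparisons the 0.008 covers, and that this level applies to the primary tests in place of the general P < 0.05. Naming a visit without this would not secure 5%.

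The cost is a few sentences in the protocol, with matching text in the analysis plan and registry entry if they do not already say so. No extra patients or visits are needed to correct this point. The downside is that effects at visits not chosen become supportive only: an early choice gives up confirmatory status for maintenance, and a late choice gives it up for the early effect.

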### Data management and monitoring

Discriminable data will be removed, replaced with the anonymised study identifier, and transferred to the principal investigator. Questionnaire data will be collected and sent to statisticians for further analysis. Data collection will be performed by trained research assistants. Access to the data will be limited to the authors and research assistants. Authors will perform data management under the responsibility of corresponding author.

During the study period, the process of each task will be periodically monitored and evaluated according to the timeline. An internet meeting consisting of the corresponding author, attending investigators, research assistants will be held to monitor the process. In this meeting, all researchers will discuss about the protocol modification, if needed.

### Sample size calculation

We assumed for sample size calculation that effective postoperative rehabilitation could restore the quality of life to a similar level before surgery. A previous lung cancer study showed that the preoperative and postoperative EQ-5D indices were 0.81 ± 0.19 and 0.74 ± 0.11, respectively [20]. Additionally, a minimal clinically important difference in EQ-5D has been observed between 0.03 and 0.05 [21]. Because patients were classified into four groups, the margin of type 1 error was set at 0.008. Calculations showed that a minimum of 76 patients in each group was required to detect a significant difference at the 0.008 level with a power of 0.9 and a dropout rate of 25%.

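### The 0.07 planning difference contrasts full with no recovery after surgery, but every arm receives rehabilitation education, so 0.07 is unsupported and probably optimistic for the add-on effect of an app

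*Protocol article*

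**What the plan says.** All references are to the protocol article.

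- **Sample size calculation, premise.** "We assumed for sample size calculation that effective postoperative rehabilitation could restore the quality of life to a similar level before surgery".
- **Sample size calculation, figures.** A previous lung cancer study is cited in which the "preoperative and postoperative EQ-5D indices were 0.81 ± 0.19 and 0.74 ± 0.11, respectively". The section adds that "a minimal clinically important difference in EQ-5D has been observed between 0.03 and 0.05".
- **Sample size calculation, error rates and size.** "Because patients were classified into four groups, the margin of type 1 error was set at 0.008". The stated result is: "a minimum of 76 patients in each group was required to detect a significant difference at the 0.008 level with a power of 0.9". The section also names "a dropout rate of 25"%.
- **Randomization and intervention.** After surgery, "all enrolled patients will participate in education sessions for pulmonary rehabilitation". Specialists teach exercise and advise on diet, and clinicians motivate and educate patients at each visit, with no restriction by group. The same paragraph says: "Patients in group D will be the control group without any intervention". The Abstract describes the fourth group in the same way and does not mention the education.
- **Background (Abstract), Discussion.** Comparing the three apps with one another is a stated aim, alongside showing that apps work.

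**The concern.** The difference that sizes the trial should be the one the randomised comparison can show. The cited figures describe quality of life before and after lung surgery. Used between arms, they mean that one arm returns to 0.81 while the other stays at 0.74, with rehabilitation as the cause of the return. In this trial the control arm also receives rehabilitation education and repeated clinician contact. What separates groups A, B and C from D is the app alone.

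Two further points follow. The level of 0.008 is close to 0.05/6, which implies all six pairs of four groups; three of those pairs are app versus app, and no effect is justified for them. The minimal important difference is quoted, but it does not drive the calculation.

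At stake are how far the 90% figure can be relied on and how a result is described. A comparison labelled as app versus no intervention would claim something other than what was randomised.

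**Working it through.** **Inputs.** Means 0.81 and 0.74, SDs 0.19 and 0.11, level 0.008, power 0.90 and dropout 25% (Sample size calculation). Two-sided tests (Statistical analysis). 320 patients allocated 1:1:1:1, so 320/4 = 80 per group (Abstract). The article prints neither the difference nor the SD used, and it does not list the contrasts. The value 0.07, the SD and the count of six below are inferences.

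**1. Implied difference.** 0.81 − 0.74 = 0.07.

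**2. Reproducing 76.** For two means, n per group = 2 × [SD × (z for 1 − α/2 + z for power) / difference]².

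- SD 0.11, α 0.008: 2 × [0.11 × (2.652 + 1.282)/0.07]² = 76.4, so 77.
- SD 0.11, α 0.05/6: 2 × [0.11 × (2.638 + 1.282)/0.07]² = 75.9, so 76.

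The stated 76 is matched by a difference of 0.07 with the smaller, postoperative SD, as an evaluable number before dropout. With 25% dropout it becomes 76/0.75, so 102 enrolled (77/0.75, so 103). With the root mean square of the two SDs, √[(0.19² + 0.11²)/2] = 0.155, the formula gives 153 evaluable. The match supports reading 0.07 as the planning effect.

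**3. Number of contrasts.** Four groups give 4 × 3/2 = 6 pairs, and 0.05/6 = 0.0083. Three pairs are app versus D and three are app versus app.

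**4. Power with the planned enrolment.** Evaluable per group: 80 × 0.75 = 60. Two-sided two-sample t-test at 0.008, noncentral t with 118 degrees of freedom, critical value 2.698, noncentrality = difference / (SD × √(2/60)). For example, 0.07 with SD 0.11 gives 0.07/0.0201 = 3.49.

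| True difference | Power, SD 0.11 | Power, SD 0.155 |
|---|---|---|
| 0.07 (planning value) | 0.78 | 0.41 |
| 0.05 (upper end of quoted range) | 0.42 | 0.18 |
| 0.03 (lower end of quoted range) | 0.12 | 0.05 |

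Simulation gives 0.42 for the 0.41 entry. A normal approximation gives slightly higher values, for example 0.80 and 0.44 for the first two entries in the SD 0.11 column.

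**5. Partial recovery in controls.** The article does not say how much of the loss controls regain through education or time, so these fractions are assumptions. If controls regain a quarter, the difference is 0.07 × 0.75 = 0.0525 and power is 0.47 (SD 0.11). If they regain half, it is 0.035 and power is about 0.18.

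**The case against.** Power is conditional on an assumed difference, and planning for an effect above the minimal important difference is not an error in itself. A reader might infer that 90% power applies to none of the six contrasts because of the mismatch. The documents do not support that step. They do not say how much controls recover, so 0.07 is unsupported for app versus control but not shown to be impossible. That power falls short even at 0.07 (0.78 with SD 0.11) is a separate matter of dropout arithmetic.

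A reader might also infer that the plan assumes zero difference between apps. It does not. The premise concerns effective rehabilitation and does not say that every app is effective. The Discussion expects the apps to work through different mechanisms and hopes to identify the best one, and an effective app could differ from an ineffective one by 0.07. Nor does the article say that the cited means come from the same patients, so the drop cannot be called within-patient.

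On the label of group D, the same paragraph makes the shared education plain, so in context the phrase means no app. That is a fair reading there, but it is not available in the Abstract. That a null result would be misread is a risk, not something the text shows.

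Finally, dividing the error rate over all pairs is valid and serves a stated aim. What stands after all this is that the section justifies 0.07 for neither kind of contrast and that the comparator is described inaccurately.

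**Conclusion.** The point holds in limited form. The difference of 0.07 represents full versus no recovery, credited to rehabilitation that all four groups receive in part. For the add-on effect of an app it is unsupported and probably optimistic; for app versus app no separate effect is justified. At the quoted minimal important difference, 60 evaluable patients per group give power between 0.12 and 0.42 with SD 0.11, and between 0.05 and 0.18 with SD 0.155, against the stated 0.90.

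These figures rest on two-sided 0.008, 25% dropout from 80 per group, a plain two-sample comparison of means, and an inferred SD; 0.11 is the one that reproduces 76. An analysis adjusted for baseline could do better, but the article gives no correlation from which to judge that. The conclusion concerns what the power statement and the comparator label can support. It does not show that the trial cannot detect a benefit.

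**What to change.** 1. In the Abstract and in Randomization and intervention, describe group D as receiving rehabilitation education and clinician motivation without an app, and word conclusions as the add-on effect of an app.
2. In Sample size calculation, state that 0.07 is an optimistic full-versus-no-recovery assumption, and restate power at 0.07, 0.05 and 0.03 with the SD and evaluable number used.

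Both are changes of wording and need no extra patients. The cost is a less favourable power statement.

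An option for the sponsor, not a required correction, is to test the three app-versus-control contrasts first at family-wise 0.05 (Holm or Dunnett) and to report app versus app as estimates with confidence intervals. In simulation with 60 per group and a difference of 0.07, Holm over three contrasts raises power per contrast from 0.79 to 0.86 (one app works) or 0.91 (all work) with SD 0.11, and from 0.42 to 0.52 or 0.60 with SD 0.155. The price is that a stated aim becomes secondary, through an amendment to the primary analysis of a trial that has been recruiting since November 2020.
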